**3.4 What are the proposed practical arrangements for allocating patients to trial groups?** We propose using a very similar mechanism to our previous leaflet trial, which used a novel method to recruit large numbers of patients. 1500 patients from each practice will be identified by the practice staff with the help of research staff. If the practices would like help (the research staff will hold honorary contracts with the PCT). Letters will be sent to patients inviting them to participate. Assuming conservatively at least 66%-70% agree to the main study (we achieved an 80% uptake previously in a similar study and using a questionnaire burden that was higher than the present study) then 1000-1100 patients in each practice should agree. If fewer agree more letters will be sent out in each practice. Patients willing to participate can return the consent form directly to the research centre, or talk with the research team before replying. Those patients wanting more explanation can also attend sessions run by the practice nurse and/or research staff as appropriate. Patients will then have time to think about the study, and can also subsequently contact the research centre later before sending their consent forms back directly to the research centre. Patients can either return the consent form by post (which has previously been the case for the majority), log on to the website to confirm consent (assuming ethics approve this method). If our pilot study indicates that a primarily postal method of trial administration is needed then the trial nurse will then provide lists of patients' numbers and details in each practice to an external randomisation line (the data will include stratification variables: age >65; influenza vaccination status; size of family, children under aged 16 living at home; access to the internet; willingness of other members of the family to use the website; attendance in the previous year with respiratory infections; a skin complaint that may affect handwashing); the randomisation centre will then randomise, stratified by the above variables, and provide the randomisation lists which will be distributed to the practice staff. The practice staff will then send out separate batches of letters to intervention patients (with the personalised website password depending on which intervention they will access) and to control patients (no password). Patients consenting to the diagnostic study will be given instructions on how to take samples, and will see a nurse for demonstration as necessary. Patients will be given the symptom diary for them to complete when an ILI develops. If the pilot study indicates that a primarily website-based method of trial administration is appropriate then randomisation will be automated and outcome measures collected electronically (with paper-based follow-up of non-respondents).

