used in previous studies, including the MRC ATEAM trial, and two vertigo trials. To reduce social desirability effects on reporting of adherence, the PETS asks patients to what extent they have been prevented from carrying out the intervention by socially acceptable reasons (e.g. symptoms too severe or aggravated by the intervention; doubts about efficacy; uncertainty about how to carry out the intervention; practical problems such as lack of time or opportunity, forgetting). They are only then asked how often and over how many weeks/months they adhered to each aspect of the intervention. To compare the effects of the intervention as a whole with the effects of the website and the target behaviours, in addition to the main intention-to-treat analysis we will carry out per protocol analyses to determine the effectiveness of the intervention in a) those who logged on to the website and b) those who reported adhering to each of the different target behaviours. We will also examine whether the website was equally effective for all sections of the target population (based on age, sex, family factors, deprivation). For the purpose of these analyses, we will supplement and validate the PETS scores using the prospective records from the web-based diary of compliance to the behaviours in each episode of family respiratory illness (completed by the intervention group only).

- **Socio-demographic and comorbidity data.** We will collect age, gender, social indices based on post code (to calculate the index of material deprivation), co-morbidities from the notes where available, and educational level from the patient. This data will document the generalisability of the sample, the similarity of trial groups, and explore effect modification due to deprivation or other demographic variables (although we did not find effect modification previously). The issue of deprivation is relevant since currently 25% of those without web access cite costs of equipment or cost of access as a contributory factor to limiting access. We will document how deprivation (measured by the index of material deprivation based on post code) relates both to uptake and effectiveness of the intervention.

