
**3.12 What is the proposed sample size?: Transmission of ILI.** All calculations are based on the patient randomised (the index person). We assume that our more rigorously developed, interactive, and tailored intervention will have an NNT of at least 25 and an OR of 0.76 - very slightly better than the previous booklets which had none of these features (OR 0.80, NNT 25). There are other reasons to assume this is a reasonable (if not conservative) effect size: people who have attended with respiratory infections are slightly more likely to be interested in participating, and in this group the effect size from previous study was significantly larger; a 20% reduction in transmission is the effect size seen in most of the studies of handwashing alone; a larger effect on behaviour is also likely given the heightened public concern about ILI since the above studies. If 10% suffer ILI (<http://www.eurosurveillance.org/em/v10n12/1012-223.asp>; <http://www.niaid.nih.gov/factsheets/flu.htm>), the average household size is 2.4 individuals (<http://www.statistics.gov.uk>) i.e. 24% can be affected by the transmission of ILI either to or from the index patient, and 20% of those with no intervention will develop ILI, then 15,074 patients are needed (assuming two-sided significance level of 5% and 80% power), or 16,000 to allow some leeway in assumptions (see table below). **Transmission of RTIs.** 16000 will have greater power to detect transmission of all RTIs, and for continuous outcomes this sample size will be extremely powerful (see table). **Nested diagnostic study.** We assume that: at least 10% of the index trial cohort will report ILI, i.e. approximately 1600; 50% will agree to the virological sub study (n=800) (based on the numbers agreeing to more intensive investigation in a current microbiological study of URTI in our group); flu virus is isolated in at least 50% of individuals presenting with ILI when ILI is circulating; and that 30-50% of patients are likely to contact the doctor then in the cohort reporting ILI then we should be able to estimate the positive predictive value of a clinical diagnosis in predicting laboratory confirmed influenza with 95% confidence intervals of +/- 10% in both the sample attending the doctor (n=240-400) and the sample not attending (n=400-560). For the analysis of the likely positive and negative predictive values (of symptoms, temperature) at each stage in the illness (12hours,24hours,36 hours etc) we will have greater precision since we can use the whole sample who agree to the diagnostic study.

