
#### Range of effect sizes likely for the trial (bold= our target for that outcome)

| Effect size                                                                                                               | N per group
(with complete outcomes where
transmission of infection possible
either to or from the index person) | Total N required for ILI
(assuming 24% where transmission
possible to or from index person; and
allowing for 20% loss to follow-up) | Total N for all respiratory
infections (assuming all cohort where
transmission possible; and allowing
20% loss to follow-up) |
|---------------------------------------------------------------------------------------------------------------------------|---------------------------------------------------------------------------------------------------------------------------|----------------------------------------------------------------------------------------------------------------------------------------------|---------------------------------------------------------------------------------------------------------------------------------------|
| Dichotomous outcomes e.g. transmission
(alpha=0.05 beta=0.2)                                                   |                                                                                                                           |                                                                                                                                              |                                                                                                                                       |
| 20% vs 18% (NNT 50; OR 0.88)                                                                                       | 6039                                                                                                                      | 62,906                                                                                                                                       | 15,098                                                                                                                         |

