| 20% vs 17% (NNT 33; OR 0.82)                                                                                              | 2629                                                                                                                      | 27,386                                                                                                                                       | 6574                                                                                                                                  |
| 20% vs 16% (NNT 25 OR 0.76)                                                                                        | 1447                                                                                                                      | 15,074                                                                                                                                | 3618                                                                                                                                  |
| 20% vs 15% (NNT 20 OR 0.71)                                                                                               | 906                                                                                                                       | 9,438                                                                                                                                        | 2266                                                                                                                                  |
| Continuous outcomes e.g. days illness
(alpha=0.01 (multiple outcomes); beta=0.1)
standardised effect sizes |                                                                                                                           |                                                                                                                                              |                                                                                                                                       |

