**Main trial analysis.** The data will be analysed according to the Statistical Analysis Plan which will be approved by the Trial Steering Committee before the commencement of any analysis. One intention to treat analysis will be performed. We will assess the transmission of ILI or other respiratory tract infection - i.e. either between the index case and family members or from family members to the index person - using multiple logistic regression, the duration of symptoms labelled moderately bad days using multiple linear regression, and attendance at the GP surgery using Poisson regression, controlling for stratifiers. We found in our previous trial of leaflets there were no significant clustering effects by practice; our analysis will be based on the index patient to avoid a design effect due to family clustering. For the symptom data the main analysis will be of symptoms in the index person but a secondary analysis will assess symptoms reported for all other family members averaged at the level of the family. Confidence intervals will be reported, and the study will be reported in accordance with the CONSORT statement.

**Subgroup analysis (using two sided 1% significance levels).** We will assess whether any of the stratification variables are effect modifiers; whether age, deprivation, education level, and co-morbidities predict outcomes or are effect modifiers; whether self reported adherence to each behaviour determines outcome.

**Diagnostic study analysis.** We will assess the sensitivity specificity likelihood ratios and positive and negative predictive values for symptoms and temperature in the whole sample, and in the sub-samples who would not contact their practice or NHS Direct (either in this or in past episodes). We will use logistic regression to determine which symptoms (and or temperature) individually or in combination are most predictive. We will also estimate the predictive value of symptoms (and or temperature) for laboratory diagnosed influenza at 12 hours after the start of the illness, then at 24 hours, 36 hours, 48 hours, and 48+ hours.

**3.20 Has a pilot study been carried out?** We have not piloted this precise protocol, but have recruited very similar trial cohorts using similar recruitment mechanisms, and have developed similar websites

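### The main models adjust only for the stratifiers, which omit practice and hold age only as over 65; a non-significant clustering test is a weak reason to ignore practice, at a small cost in efficiency

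*Protocol*

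**What the plan says.** Section 3.17-.18 of the protocol (Main trial analysis) names three main models: logistic for transmission, linear for days of moderately bad symptoms, and Poisson for GP attendance. The adjustment set is the stratifiers.

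Section 3.4 lists the stratifiers: age over 65, influenza vaccination, family size, children under 16 at home, internet access, the family's willingness to use the website, attendance with respiratory infection in the previous year, and a skin complaint affecting handwashing. Practice is not listed.

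The analysis section's one comment on practice is "We found in our previous trial of leaflets there were no significant clustering effects by practice". It does not say outright that practice is excluded from the models; that follows from the adjustment set.

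Both variables are to hand. Patients are identified and invited through their practices (section 3.4). On age, the socio-demographic paragraph of sections 3.9 and 3.10 says "We will collect age, gender, social indices based on post code".

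**The concern.** A non-significant clustering test is not evidence of no clustering. It depends on the size of the earlier trial and on the outcome tested. Section 2.4 describes that trial's result as an effect on consultation behaviour, and nothing in the protocol says that clustering was examined for transmission of infection or days of symptoms.

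Practices could plausibly differ here. GP attendance depends partly on the practice, and the trial runs in two regions. If practices start at different points of the 18-month recruitment period, practice would also carry differences between winters, though the protocol gives no schedule by practice.

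The over-65 split treats an 18-year-old and a 65-year-old alike and discards whatever age predicts within each side of the cut.

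At stake is efficiency. Outcome variation that known baseline variables could explain is left unexplained.

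**Working it through.** **Inputs from the protocol.** Section 3.12 sizes the trial "assuming two-sided significance level of 5% and 80% power". The table row is "20% vs 16% (NNT 25 OR 0.76". It takes it that "24% can be affected by the transmission of ILI either to or from the index patient", and the total is after "allowing for 20% loss to follow-up". The result is "then 15,074 patients are needed", raised to 16,000. Section 3.4 expects 1,000 to 1,100 patients per practice.

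**Assumptions.** The protocol gives no ICC for practice and no R² for age. I take ICC 0.001 to 0.05 and age R² 0.01 to 0.05.

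**1. Reproduce the stated sample size.**

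n per group = [1.960·√(2·0.18·0.82) + 0.842·√(0.20·0.80 + 0.16·0.84)]² / 0.04² = 1,447, as in the table.

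Total = 2 × 1,447 / 0.24 / 0.80 = 15,073. Rounding each group up (7,536.5 to 7,537) gives the stated 15,074.

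With 16,000 enrolled, 16,000 × 0.80 × 0.24 / 2 = 1,536 per group, and power is 82.3%.

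**2. Number of practices.** 16,000 / 1,100 = 14.5 and 16,000 / 1,000 = 16, so about 15 to 16.

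**3. Adding practice, linear approximation.** Adjustment multiplies the variance of the treatment effect by about (1 − ICC). Power = Φ(2.802/√(1 − ICC) − 1.960).

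| ICC (assumed) | Equivalent N, 15,074 × (1 − ICC) | Patients' worth | Power |
|---|---|---|---|
| 0.001 | 15,059 | 15 | 80.0% |
| 0.01 | 14,923 | 151 | 80.4% |
| 0.02 | 14,773 | 301 | 80.8% |
| 0.05 | 14,320 | 754 | 82.0% |

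**4. Age in years in place of the split, linear approximation.** The variance factor is (1 − R²)/(1 − R²·s), where s is the share of age's R² that the split keeps. For a linear age effect, s is 0.63 if age is uniform on 18 to 85 and 0.47 if age is about normal (mean 50, SD 16).

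- R² 0.01, s 0.63: 15,074 × 0.990/0.9937 = 15,018; power 80.2%.
- R² 0.05, s 0.47: 15,074 × 0.950/0.9764 = 14,667; power 81.1%.

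**5. Logistic simulation of ILI transmission.** 2,894 patients analysed (2 × 1,447), 16 practices, allocation balanced within practice, 600 data sets per setting. The current model has treatment and age over 65. The fuller model has treatment, age in years and practice indicators.

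| Latent ICC | Power, current | Power, fuller | Log OR (SE), current | Log OR (SE), fuller |
|---|---|---|---|---|
| 0 (no age effect) | 80.7% | 81.0% | −0.272 (0.0973) | −0.273 (0.0975) |
| 0.01 | 79.2% | 79.3% | −0.266 (0.0971) | −0.269 (0.0976) |
| 0.02 | 79.5% | 79.8% | −0.265 (0.0966) | −0.270 (0.0974) |
| 0.05 | 80.3% | 81.0% | −0.262 (0.0957) | −0.271 (0.0973) |

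The gain is under 1 point throughout. At latent ICC 0.01 and 0.02 it is no larger than the 0.3 points seen with no practice or age effect at all. The standard error does not fall; it rises slightly. The gain comes from the log odds ratio moving away from zero: at 0.05 the ratio of estimate to standard error goes from 0.2617/0.0957 = 2.73 to 0.2706/0.0973 = 2.78.

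The latent ICC is on the logit scale. A practice SD of 0.42 (latent ICC 0.05) corresponds to roughly 0.42² × 0.18 × 0.82 = 0.026 on the observed scale, for which the formula in step 3 gives about 1 point. The two approaches agree.

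**6. Type I error.** With no treatment effect (1,000 data sets each), the current model rejected in 4.9% (latent ICC 0.02) and 3.9% (0.05). Simulation error is about √(0.05 × 0.95/1,000) = 0.7 points. There is no inflation.

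No calculation was made for the Poisson model.

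**The case against.** The strongest reply is that the analysis is to follow a separate SAP, which is not at hand and could include practice and age in years. That limits the point but does not remove it: the protocol itself names an adjustment set and offers an argument about practice, and that argument is weak as it stands.

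The second reply is that the gain is small. This stands. Enrolling 16,000 rather than 15,074 already takes power to 82.3%, more than either change adds on its own in the ranges above.

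Four stronger readings are tempting and not supported:

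- *Allocation is made within practice, so the model ignores the design.* Sending patients' "details in each practice to an external randomisation line" applies only if the pilot favours postal administration. Even then the stratification is by the listed variables, and practice is not one. On the website route randomisation is automated and practice lists are not mentioned.
- *Age is used nowhere except as over 65.* That is true of the stratifiers. The subgroup paragraph also examines age as a predictor and effect modifier, without that cut.
- *Household size is grouped.* Section 3.4 lists family size and gives no grouping.
- *Standard errors would fall for all three outcomes.* The (1 − ICC) argument belongs to the linear model. For logistic transmission the simulation shows no fall.

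**Conclusion.** The point holds as a minor matter of efficiency. The main models adjust for stratifiers that omit practice and carry age only as a split at 65, and the single argument offered on practice does not support treating practices as alike for these outcomes.

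The size is about 0.4 to 2.0 power points for practice (ICC 0.01 to 0.05) and 0.2 to 1.1 for age in years, by the linear approximation. For the logistic transmission outcome, the two together gain under 1 point. These figures rest on assumed ICCs, age effects and age distributions; the age figures also assume a roughly linear effect.

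A reader might infer that ignoring practice makes the comparison biased or the test too liberal. It does not: patients, not practices, are randomised, and the simulated error rate of the transmission test stayed at or below 5%.

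**What to change.** - In section 3.17-.18, delete the earlier trial's non-significant clustering result as the reason to ignore practice.
- State there, and in the SAP, that the main logistic, linear and Poisson models include practice (fixed or random effect) and age in years in place of the over-65 split, alongside the other stratifiers.
- Say that the logistic odds ratio is then conditional on these terms. In the simulation at latent ICC 0.05 it moved from exp(−0.262) = 0.770 to exp(−0.271) = 0.763.

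The cost is a sentence or two and no new data. Fixed effects use about 15 parameters. Even for ILI transmission that is affordable: 16,000 × 0.80 × 0.24 = 3,072 analysable patients, or 192 per practice with 16 practices, and about 35 events in each at an average risk of 18%. The choice should be made before any outcome is analysed.

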## **5.1 Financial summary TOTAL**

|                                 |            |
|---------------------------------|------------|
| Research costs                  | £1,204,871 |
| TSC/DMEC costs                  | £1,800     |
| Trial Registration costs (£200) | £200       |
| NHS Treatment costs             | £697,140   |

**6.1 Application history.** This application falls under the clinical trials and influenza calls. The cross board group considered the outline, supported the main trial and virological study, but asked us to consider:

- 1) lengthening the recruitment rate and support follow-up; we have added 6 months to the recruitment time; in our previous study we recruited practices and completed follow-up in 2 years for 4000+ patients with a lower level of resourcing per practice recruited and patient recruited ; adding a further 6 months allows for the increased difficulties in the current climate, and we have also increased clerical support modestly to aid with follow-up in the final year (this is now altogether more than 50% more resource available for notes review per patient recruited and over a 50% longer time period than we used in our previous trial); we can add a further 6 months if the Board desires (but that will require another 6 months staff time pro rata)
- 2) providing more details for the development phase (particularly survey methodology and objectives): we have provided more details of the development phase which will be led by [name]
- 3) providing more details of the latest evidence base for the nature and impact of the behavioural change envisaged : we have completed our Cochrane review of the use of patient information in self limiting illness including influenza; we have augmented the discussion of the latest reviews of the evidence base for the nature and impact of the likely behavioural change; the most well documented behaviour is hand-washing which from the limited range of existing studies probably has a slightly greater effect in preventing transmission than our proposed effect size; thus we will concentrate on hand-washing as the primary behaviour of interest; there is less evidence for the other behaviours but all are included as part of both national and international guidance and are plausibly likely to have additional impact to hand-washing
- 4) setting out clear intermediate milestones/deliverables so that the feasibility and relevance of the RCT could be assessed: we have provided three key deliverables related to the development of the intervention and propose that if the last Key deliverable (i.e. deliverable 3)- i.e. the change in attitudes and intentions based on the pilot study - is not met, then the main RCT does not continue
- 5) limiting the patients to those with web access; we have modified the protocol to accommodate this; although the number of families with web access is rapidly increasing year on year (last year 60%) there may well still be issues of equity of access to the web based on financial considerations; we will deal with this in both secondary analysis (by estimating whether index of deprivation is related to uptake of the offer of invitation to participate and whether it modifies the effect sizes); we can also explore encourage participation by encouraging web access from local libraries for those families that do not have access to the web at home; finally we will develop a booklet form of the intervention, and although we will not evaluate it separately as part of this trial, it could potentially be made available for families with no access to the web.

Reference List.

(1)[http://www.who.int/csr/resources/publications/influenza/WHO\\_CDS\\_CSR\\_GIP\\_2005\\_5.pdf](http://www.who.int/csr/resources/publications/influenza/WHO_CDS_CSR_GIP_2005_5.pdf). WHO publications 2005.

(2) Zambon M, Stockton J, Clewley J, Fleming DM. Contribution of influenza and respiratory syncytial

virus to community cases of influenza-like illness: an observational study. *Lancet* 2001; 358 (9291):1382-1383.

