#### **Main trial:**

Adult patients (aged 18+) living with at least one other person. Patients whose GP notes show a skin problem that may affect handwashing ability, and those who live in households where no one else is willing to provide illness feedback will be excluded. Participants will be randomised to:

- 1) Access to an interactive website by a personal password, providing tailored advice; this will be reinforced by email prompts and reminders to use the website; patients will be advised to use hand-washing and a range of infection control measures both within and outside the family
- 2) Normal care (access to the website at the end of the trial)

**Outcomes:** transmission of ILI and other infections between family members, severity and duration of ILI and other respiratory infections.

**Virological sub study:** based on laboratory confirmed virological diagnosis, we will document the nature of circulating viruses, estimate whether transmission differs according to the type of viral illness; provide estimates of the predictive value of clinical symptoms and signs according to the spectrum of illness (defined by contact with the NHS and prior duration of illness).

**3.2 What is the proposed trial design.** An RCT, with a development phase and a nested viral study.

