
**3.5 Methods of protecting against bias (e.g. masking, blinding)?** Blinding of patients to whether they have

received the intervention is impossible. Data entry will be blind to study group. Selection bias and non-response/loss to follow-up bias will be assessed by comparing the socio-demographic/clinical characteristics of those recruited/not recruited and followed up/not followed-up respectively. **Selection bias:** We will document when eligible patients are not entered into the study, the reason why, treatment, and clinical characteristics.

**3.6 Inclusion criteria.** Adult patients (aged 18+) from GPs computerised lists where there is at least another living in the household. **Exclusion criteria.** Patients with severe mental problems (e.g. major uncontrolled depression/schizophrenia;dementia;severe mental impairment - unable to complete outcomes) or terminally ill. Patients who have reported a skin complaints that may affect their ability to wash their hands. Participants who live in a household where no one else is willing to provide information on illnesses via the website.

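### Section 6.1 says entry is limited to people with web access, but the entry criteria do not require it of the index person and one randomisation route still stratifies by internet access

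*Protocol*

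**What the plan says.** - **6.1, item 5 (application history).** In response to the funder, the protocol reports "limiting the patients to those with web access; we have modified the protocol to accommodate this". It adds that library access could be explored for families without the web at home, and that a booklet form will be developed but not evaluated separately in this trial.
- **3.1, main trial.** Entry is open to "Adult patients (aged 18+) living with at least one other person". On household reporting, "those who live in households where no one else is willing to provide illness feedback will be excluded".
- **3.6.** Inclusion reads "Adult patients (aged 18+) from GPs computerised lists where there is at least another living in the household". The exclusions include "Participants who live in a household where no one else is willing to provide information on illnesses via the website". Web or email access of the index person is not mentioned. Both 3.1 and 3.6 exclude a skin problem that may affect handwashing.
- **3.4.** The only list of stratifiers is introduced by "If our pilot study indicates that a primarily postal method of trial administration is needed". It includes "access to the internet; willingness of other members of the family to use the website", and also a skin complaint affecting handwashing. For the other route the text says "If the pilot study indicates that a primarily website-based method of trial administration is appropriate then randomisation will be automated", with outcomes collected electronically and no stratifiers listed.
- **3.17-.18.** The main analysis is by intention to treat and controls for the stratifiers. The subgroup analysis tests each stratifier as an effect modifier.
- **3.12 and its table.** The ILI target is 20% versus 16%, with 24% of patients in a position where transmission is possible and 20% loss to follow-up. This gives 15,074 patients, raised to 16,000.

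**The concern.** The experimental arm is a password-protected website reinforced by email (3.1, 3.3). An index person who cannot get online cannot personally receive it. Section 6.1 says the protocol now deals with this by restricting entry, but staff who screen and randomise will work from 3.1, 3.4 and 3.6. Those sections do not carry the restriction for the person being randomised, and the stratifier list in 3.4 reads as though access still varies among participants.

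Two things are at stake. First, under intention to treat, anyone allocated to a website they cannot reach counts in the intervention arm while contributing little or no effect, and the assumed 20% versus 16% makes no allowance for that. Second, the stratification and adjustment set would carry variables with a single value: the skin complaint once the exclusion is applied, and internet access if the restriction in 6.1 is applied.

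**Working it through.** **Setting the sections side by side**

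| Section | Web access of index person | Related condition |
|---|---|---|
| 6.1, item 5 | Said to be required | Library access may be explored |
| 3.1 | Not mentioned | Another household member must be willing to give illness feedback; website not named |
| 3.6 | Not mentioned | Another household member must be willing to report through the website |
| 3.4, postal route | Treated as a stratifier | Skin complaint also a stratifier |
| 3.4, website route | No stratifiers listed | Automated randomisation, electronic outcomes |

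Only 6.1 states the restriction. The condition in 3.6 screens indirectly, through someone other than the index person, and 3.1 does not repeat its web element.

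**Reproducing the plan's figure**

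Inputs from 3.12: p1 = 0.20, p2 = 0.16, two-sided alpha 0.05, power 80%. With pooled variance under the null and no continuity correction,

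n = [z(0.975)·√(2·p̄·(1 − p̄)) + z(0.80)·√(p1(1 − p1) + p2(1 − p2))]² / (p1 − p2)²

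where p̄ = (0.20 + 0.16)/2 = 0.18:

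n = [1.960 × √0.2952 + 0.842 × √0.2944]² / 0.0016, which gives 1,447 per group, as in the table.

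Total = 2 × 1,447 / 0.24 / 0.80 = 15,073, against 15,074 stated, a rounding difference. The sample size is therefore right on its own inputs.

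**Size of a possible dilution**

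At 16,000 patients the number per group with complete outcomes and transmission possible is 16,000 × 0.24 × 0.80 / 2 = 1,536.

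Let f be the share of randomised people who cannot reach the website. The protocol does not give f, so it is an assumption here, as is a zero effect in those people. The intervention-arm rate becomes

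p2(f) = 0.20 − 0.04 × (1 − f)

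and power is Φ{[(p1 − p2)·√n − 1.960·√(2·p̄·(1 − p̄))] / √(p1(1 − p1) + p2(1 − p2))} with n = 1,536.

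| f | p2 | Difference (points) | Power at 16,000 | Total for 80% power |
|---|---|---|---|---|
| 0% | 16.0% | 4.0 | 82% | 15,074 (stated) |
| 5% | 16.2% | 3.8 | 78% | about 16,780 |
| 10% | 16.4% | 3.6 | 73% | about 18,780 |
| 20% | 16.8% | 3.2 | 63% | about 23,970 |

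The totals come from the same formula (1,611, 1,803 and 2,301 per group), doubled and divided by 0.24 and 0.80. The 10% and 20% rows are the complement of the 80-90% home access that 3.3 thinks possible by the end of the trial. That is a population figure and not an estimate for consenting participants.

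**The case against.** The other side has several good points.

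- **3.6 does contain a web condition.** A household in which nobody else will report through the website is excluded, so many households with no access would drop out. This stands as a partial screen. It does not test the index person, and 3.1 omits the website from the same exclusion.
- **Other text presumes web or email use.** Section 3.3 sends email prompts to all patients when influenza circulates, and 3.9/3.10 gives those who choose paper sheets the monthly email reminders. This shows the intention but does not make access an entry criterion.
- **The stratifier list is conditional.** A reader might infer that randomisation will be stratified by internet access in any case. The documents do not support that: the list belongs to the postal route only. The entry criteria, however, apply under both routes.
- **Internet access might still vary among eligible people.** With library use in view, the stratifier could separate home from other access. That is possible, but 3.4 does not say so. A stratifier that is truly constant does no harm beyond clutter.
- **Section 6.1 is an application history.** True, but it describes what the protocol now does, so the operative sections should agree with it.

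A reader might also infer that loss to follow-up has been overlooked. It has not: 20% is allowed for, and there are paper diary sheets, paper follow-up of non-respondents and an end-of-winter questionnaire.

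**Conclusion.** The inconsistency is real. Section 6.1 claims a restriction that 3.1 and 3.6 do not impose on the index person, and 3.4's postal route stratifies by a variable that the restriction would make constant. It also stratifies by a skin complaint that the exclusions already remove. Followed as written, the protocol could randomise people to a website they cannot reach.

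The size of the consequence is unknown. If 5% to 20% lacked access and gained nothing, power for ILI transmission at 16,000 would be 78% to 63% instead of 82%, so a share as small as 5% would take it below the planned 80%. Self-selection into a website trial, the exclusion in 3.6, library use and website use by other household members would all reduce the loss.

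A reader might go further and conclude that the effect will be diluted, that the sample size is wrong, or that access of just over 60% implies 30% to 40% of participants without it (power 51% to 40%). The documents do not support these conclusions. They give no share among those randomised, the calculation reproduces, and the household figure in 3.3 is more than 60%, rising, and not specific to people who agree to take part.

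**What to change.** Reconcile 3.1, 3.4, 3.6 and 6.1:

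1. Add web and email access of the index person, checked before randomisation, to the inclusion criteria in 3.1 and 3.6.
2. State whether library or other access outside the home counts.
3. Use one wording for the household-reporting exclusion in 3.1 and 3.6, saying whether reporting must be through the website.
4. Remove the skin complaint from the stratifiers in 3.4 and from the adjustment set in 3.17-.18.
5. Remove internet access from both as well, or redefine it as home versus other access.

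The cost is a wording change to eligibility and stratification, plus one screening question. Entry becomes slightly narrower, which 6.1 already accepts, and the planned 16,000 need not change.
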